# 1. PROTOCOL SUMMARY

## 1.1. Synopsis

Title: Electronic pillbox-enabled self-administered therapy versus standard directly observed therapy for tuberculosis medication adherence and treatment outcomes in Ethiopia: a multicenter randomized controlled trial (SELFTB trial)

Hypothesis: The use of a digital medication event reminder and monitor device-observed self-administered therapy provides non-inferior medication adherence and treatment outcomes for patients with TB compared with the standard in-person directly-observed therapy (DOT) in Ethiopia, one of the low-income countries with the highest burden of TB.

Objectives: Primary objectives:

1. To assess whether a digital medication event reminder monitor (MERM) device-observed self-administered therapy improves adherence in patients with TB compared with the standard DOT.
2. To assess whether MERM-observed self-administered therapy improves treatment outcomes in patients with TB compared with the standard DOT.

Secondary objectives:

3. To evaluate if MERM-observed therapy provides higher health-related quality-of-life (HRQoL) and lower catastrophic costs compared to the standard DOT
4. To evaluate the patient-reported usability and treatment satisfaction with MERM-observed self-administered TB therapy compared with the standard in-person DOT.

Outcome measures: Primary outcomes:

1. Level of adherence: Individual-level percentage adherence over the two-month intensive phase measured by adherence records compiled from MERM device vs. DOT records.
2. Sputum conversion: Participants with sputum smear converted following the standard two-month intensive phase treatment.

Secondary outcomes

3. Negative IsoScreen urine isoniazid test: Participants having at least one negative urine isoniazid test result (IsoScreen test, GFC Diagnostics Ltd, Bicester, England)

4. Adverse treatment outcome: Participants having at least one of the three events: treatment not completed; death; or loss to follow-up
5. Self-reported adherence: Participants who self-reported to have forgotten to take their medication
6. Health-related quality of life (HRQoL): The association between MERM-observed therapy and HRQoL, with the HRQoL measured and calculated for each participant by arm using the EuroQoL 5-dimension 5-level (EQ-5D-5L) score ranging from 0 to 1, with a higher score designating better HRQoL.
7. Catastrophic costs: Participants with overall TB treatment cost exceeding or equivalent to 20% of their income.
8. Post-diagnostic cost from an individual patient's perspective: Participant's cumulative direct costs (out-of-pocket costs related to anti-TB drug pick-up) and indirect costs (guardian and coping costs) over the two-month intensive phase.
9. Patient-reported treatment satisfaction: Participant's treatment satisfaction measured using the treatment satisfaction questionnaire for medication version 1.4 (TSQM v1.4) tool on a scale from 0 to 100, with a higher score indicating better satisfaction.
10. Patient-reported usability of the MERM device: Participant's experience using the MERM device measured by an 18-item questionnaire and the score transformed into a scale from 0 to 100, with a higher score indicating better usability (Intervention arm only).

**Methods:** *Design:* A multicenter, randomized, controlled, open-label, non-inferiority, effectiveness-implementation type 2 hybrid trial in ten healthcare facilities in Addis Ababa, Ethiopia. The study will not dictate diagnosis and treatment for TB; thus, it will not introduce or use new medications.

*Setting:* The study country is Ethiopia – a high TB-burden, low-income country located in sub-Saharan Africa. In Addis Ababa, a total of 94 public health centers provide TB care and treatment services under the DOT program. This study stratifies the 94 health centers on the bases of the 10 sub-cities where they are located. From each stratified group, one health center with the largest TB client load will be selected, with a total of 10 health centers to be included. Health management information system (HMIS) quarterly data (April 01 - June 30, 2019) taken from the Addis Ababa Regional Health Bureau will be used for the purpose.

*Participants:* The source population will be all new patients with TB symptoms who come to a study site and undergo bacteriological screening during the study period or TB patients bacteriologically confirmed elsewhere and referred to a study site for TB treatment. Inclusion criteria: i) patients with new, or previously treated, bacteriologically-confirmed drug-sensitive pulmonary TB, ii) eligible to start the

standard 6-month first-line anti-TB medication, iii) outpatient status at the time of screening and enrollment, iv) men or women age  $\geq 18$  years, and v) able and willing to provide informed consent. The sample size calculation yields a sample of 57 in each arm for a total of 114 participants.

**Intervention:** Participants will be randomly assigned (1:1) to receive a 15-day TB medication supply in the evriMED500® MERM device to self-administer and return every 15 days (intervention arm) or the standard in-person DOT (control arm). Both will be followed throughout the standard two-month intensive treatment phase (2RHZE). The MERM device has an electronic module and a medication container that records adherence, stores medication, emits audible and visual on-board alarms to remind patients to take their medications on time and refill, and enables providers to download the data and monitor adherence.

**Study Duration:** The study duration is 12 months from opening enrollment until completion of data analyses. Participant duration is 2 months for each individual participant to complete all visits.

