## **6.2. Secondary outcomes**

### **6.2.1. Negative IsoScreen urine isoniazid test**

- Number of participants with negative IsoScreen urine isoniazid test.

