### **8.6. Interventions**

Participants in the intervention arm will receive a 15-days TB medication supply (HRZE fixed-dose combination therapy of 15 doses) in an electronic pillbox device (evriMed500 digital medication monitoring and reminder device manufactured by Wisepill Technologies, South Africa) to self-administer. Providers will collect baseline data, including demographic, socioeconomic, behavioral, and social factors using the study's baseline questionnaire. Based on the baseline data, participants will be clustered into four behavioral determinants (use cigarettes, alcohol, Khat - a psychostimulant plant, and cocaine/marijuana) and three social determinants (homeless, unemployed, and illiterate) as appropriate for the purpose of analysis. Participants in this arm will return every 15 days, where the provider will count any remaining tablets in the pillbox, download the pill-taking data from the Wisepill device, evaluate the functionality of the device and troubleshoot as needed, and perform the urine

isoniazid test. The level of adherence in their intensive phase of treatment will be calculated using the medication possession ratio (MPR). Any participant who misses more than five tablets in any 15- day refills will be reassigned to daily DOT throughout the remaining days of the intensive phase. Participants in the intervention arm can consult the healthcare provider in cases of medical illness or any adverse events outside of a scheduled visit before the next appointment. The phone number of the healthcare provider following their TB condition will be written at the backside of their appointment cards. The phone call strategy aims to maintain the DOT advantage for the intervention arm.

Participants in the control arm will get their treatment as per the standard practice of DOT, where participants will visit the healthcare facility each business day throughout the two months intensive phase to swallow their daily dose of HRZE with direct observation by the healthcare provider. Additionally, they will be given pills for the weekend to take them at home. The provider will collect baseline data, conduct a urine isoniazid test every 15-days, and cluster participants into behavioral and social determinants as applicable for participants in the intervention arm. For this arm, the management of participants who interrupt treatment will follow the national TB treatment guidelines.

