For the laboratory research involving biological specimens (urine and sputum), the study will use WHO-approved diagnostic tools. The IsoScreen test is a semi-quantitative urine test that provides a reliable and immediate indication of adherence to isoniazid-containing treatment regimens for patients with TB. It uses the reagents of the Arkansas Method: barbituric acid (20 mg), potassium cyanide (10 mg) and chloramine-T (10 mg), in an enclosed plastic testing device for safe and rapid testing in clinics and patients' homes. A urine sample is added to the plastic testing device. If the sample develops a blue color, it is positive for isoniazid metabolites and is therefore from a patient who is compliant with the treatment. A blue/purple color indicates that the drug was taken within the last 24 hours. A green color

also indicates isoniazid metabolites, but the drug was probably taken about 48 hours ago. If the sample remains yellow, then the patient is not adhering to their daily treatment. The providers will perform this test within the study facilities for both arms every 15 days, thus four times per participant. Sputum specimens collected before and after the intensive phase. Under the routine practice, the sputum samples will be tested for Acid-fast bacilli (AFB) microscopy to check for sputum smear conversion following the intensive phase. Initiation, termination or completion of treatment will rely only on the standard procedures available at the study sites, which could be acid-fast bacilli or Xpert MTB/RIF assay. Thus, the outcomes of the study's laboratory results will not dictate the standard diagnostic or treatment procedures.

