## **9. STATISTICAL ANALYSIS**

Descriptive summary measures will be used to report participant characteristics. Chi-square tests will be used to evaluate potential associations among categorical variables. To compare the level of adherence between study arms and among variables, independent t-tests will be done on log-

transformed adherence percentage of the expected 60 days. Effects of the arms and other adherence variables will be estimated using a geometric mean (GM) with geometric standard deviation (GSD) and mean ratios (MR) with 95% confidence intervals (CI). Log binomial regression will be conducted to identify risk factors of at least one negative isoniazid urine test and self-reported adherence of participants. Effects will be measured using adjusted relative risk (ARR) with 95%CI. A general linear model will be done on log-transformed adherence percentage to identify the effects of variables on participants' level of adherence. Effects will be measured using an adjusted mean ratio (AMR) with 95% CI.

Descriptive statistics including frequency and percentage will be used to describe the health state of the study participants. Multiple bar charts with cross-tabulation will be used to illustrate distributions of health states by study arms. Chi-square and Fisher's exact tests will be employed to compare the five EQ-5D-5L health domains by study arms. Kolmogorov–Smirnov, Shapiro–Wilk tests, and median values with interquartile range (IQR) will be used to summarize EQ-5D-5L index value/utility. Nonparametric Mann–Whitney U test will be employed to compare the difference in EQ-5D-5L index value/utility among study arms. A log-binomial model will be used to identify risk factors for lower HRQoL, which is having at least one health problem.

The overall TB treatment cost will be estimated by considering costs related to anti-TB drug pick-up, guardian costs, and coping costs over the two-month intensive phase. The proportion of study participants who faced catastrophic costs at a cut-off point of 20% will be estimated. A cross-tabulation will be employed to evaluate the distribution of catastrophic cost over the study arms and chi-square test will be used to test the association between catastrophic cost and study arms.

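### The urine isoniazid outcome leaves between-arm comparability unprotected: an untaken test cannot be negative, and control sampling is not placed before the witnessed dose

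*Protocol*

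**What the plan says.** The synopsis (Protocol 1.1) defines the outcome as "Participants having at least one negative urine isoniazid test result". Section 6.2.1 words it differently, as "Number of participants with negative IsoScreen urine isoniazid test", and so drops the at-least-one rule. Section 9 analyses the synopsis form: "Log binomial regression will be conducted to identify risk factors of at least one negative isoniazid urine test".

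On conduct, section 8.7 states: "The providers will perform this test within the study facilities for both arms every 15 days, thus four times per participant". It also describes how the assay is read. "A blue/purple color indicates that the drug was taken within the last 24 hours"; a green colour "also indicates isoniazid metabolites, but the drug was probably taken about 48 hours ago"; and "If the sample remains yellow, then the patient is not adhering to their daily treatment". The result therefore reflects roughly the last one to two days.

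In the control arm (section 8.6), participants attend each business day "to swallow their daily dose of HRZE with direct observation by the healthcare provider" and take weekend doses at home. In the intervention arm they self-administer and are tested at a return visit every 15 days. Neither 8.6 nor 8.7 says whether the control sample is taken before or after that day's observed dose, and neither asks for the time since the last dose. The protocol gives no rule for a test that is not done.

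**The concern.** The primary adherence outcome compares two different instruments, a pillbox log and DOT records, in an open-label trial. The urine assay is the same in both arms and is the only biological adherence measure described. Section 7 relies on electronic, self-reported and biological measures together to make the adherence result credible. What this outcome can and cannot show therefore matters more than its secondary rank suggests.

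There are two mechanisms:

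- **Number of tests.** Under an at-least-one-negative rule, each test is one chance to be counted as non-adherent. Someone who stops attending has fewer chances, and may look better on this outcome than someone who attends all four visits.
- **Timing of the sample.** If a control participant gives urine after swallowing that day's witnessed dose, the result may show only that they attended that day. Misses on the preceding days could go unseen. Intervention participants have no witnessed dose, unless they have been moved to daily DOT under section 8.6, after which their later tests are taken under DOT as well.

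**Working it through.** **Inputs from the protocol.** Four planned tests per participant (8.7); a reading window of about 24 to 48 hours (8.7); 10% attrition and 79% mean adherence (8.5.1.5).

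**Assumptions, because the protocol gives no figure.** The per-test risk of a negative, p, is taken as 5%, 10% or 21% (the last is 100% minus 79%). Tests within a person are independent. The share m of tests masked by a recent dose is varied. A masked test is assumed unable to be negative; the protocol does not say how soon after a dose the assay turns positive.

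**Plan's own figure.** None is given for this outcome. The stated size is for percentage adherence: 2 × [0.36 × (1.960 + 0.842) / 0.20]² = 50.9, so 51 per arm; 51 / 0.90 = 56.7, so 57 per arm. It reproduces, and this point does not affect it.

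**Step 1: one participant with k tests done.** Risk of at least one negative = 1 − (1 − p)^k.

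| p | k = 4 | k = 3 | k = 2 | k = 1 | 2 tests ÷ 4 tests |
|---|---|---|---|---|---|
| 5% | 18.5% | 14.3% | 9.8% | 5.0% | 0.53 |
| 10% | 34.4% | 27.1% | 19.0% | 10.0% | 0.55 |
| 21% | 61.0% | 50.7% | 37.6% | 21.0% | 0.62 |

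**Step 2: a whole arm, p = 10%.** Suppose 10% of one arm have an incomplete series and everyone else has four tests.

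- Two tests each: 0.9 × 34.4% + 0.1 × 19.0% = 32.9%, a ratio of 0.96 to the complete arm.
- One test each: 0.9 × 34.4% + 0.1 × 10.0% = 32.0%, a ratio of 0.93.
- The same loss in both arms: ratio 1.

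**Step 3: masking, equal true adherence, four tests done.** Risk = 1 − (1 − p(1 − m))^4.

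| p | Unmasked | m = 25% | m = 50% | Unmasked ÷ 25% | Unmasked ÷ 50% |
|---|---|---|---|---|---|
| 5% | 18.5% | 14.2% | 9.6% | 1.31 | 1.93 |
| 10% | 34.4% | 26.8% | 18.5% | 1.28 | 1.85 |
| 21% | 61.0% | 49.6% | 35.8% | 1.23 | 1.70 |

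If only control tests are masked, the last two columns are false relative risks against the intervention. The intervention arm can be masked too, by a dose taken shortly before a known visit. At p = 10%:

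- 50% masked in control and 25% in intervention: 26.8 / 18.5 = 1.44.
- 25% masked in control and 50% in intervention: 18.5 / 26.8 = 0.69.
- Equal shares: 1.

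The sign depends on shares that the protocol does not allow anyone to estimate.

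**Step 4: what a pre-dose sample would read.** On most weekdays it reflects the previous business day's witnessed dose, which falls inside the window. After a weekend the last witnessed dose is about three days old, outside the window, so the sample reads the home doses. It can also show a participant who missed the preceding days and then returned; a sample taken after the dose may not.

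**The case against.** The case on the other side is substantial.

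- **Design symmetry.** Place, interval and number of tests are the same in both arms. Classifying a participant by any negative result is a legitimate endpoint, and a rule for missed tests is commonly left to a SAP, which is not at hand. This stands: the absence of a missed-test rule is not by itself an error.
- **Non-attenders show up elsewhere.** Section 6.2.2 counts non-completion, death and loss to follow-up, and section 9 takes adherence as a percentage of 60 expected days. This stands too; the gap is confined to the urine outcome.
- **Direction.** A reader might infer that fewer tests flatter the intervention, because control participants attend every business day while intervention participants come only every 15 days. The protocol does not support this: it gives no attendance by arm, and section 2.1 itself describes daily DOT as irregular in practice.
- **Size.** A reader might also infer that losing half the tests would nearly halve apparent non-adherence in the trial. That holds for an individual (step 1) but not for an arm with losses near the stated 10% attrition (step 2). Positive correlation between a person's tests would weaken the dependence on test number further.
- **Sampling order.** Pre-dose sampling changes little on most weekdays (step 4), and intervention visits are predictable. So the arms cannot be called non-comparable; what can be said is that comparability is not protected.

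The timing gap itself remains. The order of sampling and the time since the last dose are site procedures, and if they are not fixed and recorded during conduct no later analysis plan can recover them.

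**Conclusion.** The point holds as a modest, inexpensive improvement. As defined, an untaken test can never count against a participant, and a same-day witnessed dose may mask recent misses in the control arm.

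The first mechanism is large for an individual (34% with four tests against 19% with two, at an assumed independent 10% per test) but small for an arm (34.4% against 32.9% if 10% of one arm have two tests). The second could be larger: a false relative risk of 1.23 to 1.93 if a quarter to a half of control tests, and no intervention tests, were masked. Those shares are assumptions, and predictable intervention visits could offset or reverse the effect. The net direction is unknown.

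This is a secondary outcome. The primary analysis and the sample size of 57 per arm are untouched.

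**What to change.** 1. In sections 8.6 and 8.7, state that control-arm urine is collected on arrival, before that day's observed dose. This sets the order of sampling only.
2. Add a field to the follow-up form, in both arms, for hours since the last dose.
3. Report tests done out of four, by arm.
4. Keep the at-least-one-negative outcome, and add a sensitivity analysis that counts a missed test as negative.
5. Add a supportive per-test analysis: a log-link GEE of a negative result on arm and visit, clustered by participant. It uses all four results and shows the pattern by visit, but does not by itself correct for missed tests; item 4 is what addresses those.
6. Make section 6.2.1 match the synopsis.

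The cost is one form field, one instruction on sampling order and a little more analysis. No extra visits or tests are needed.

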## 1.2. Scheme

[figure not shown]

**Figure 1:** Schematic diagram of the study

## **2. BACKGROUND**

### **2.1. Study rationale**

The World Health Organization (WHO) revealed its commitment to tuberculosis (TB) patients in its End TB strategy that “everyone with TB should have access to the innovative tools and services they need for rapid diagnosis, treatment, and care; this is a matter of social justice, fundamental to our goal of universal health coverage”. This commitment is a collective responsibility towards human rights; making sure that no family is burdened with avoidable death or catastrophic expenses due to TB by 2030. However, taking pride in the slogan “End TB by 2030” is insufficient for true progress. In order to translate aspirational goals into reality, practical solutions should be sought. The strategy might appear to be a zero-sum if interventions on the disease neglect key socioeconomic burdens that individual patients are incapable of avoiding. The association between TB and poverty is a reality, but the disease is a global health security threat that urgently needs collective resources for mutual welfare. In the last three decades, different strategies and care packages have been formulated and implemented to halt the disease. However, improvements are not as expected; instead, a drug-resistant form of the disease is spreading, with globalization and migration fueling multiple strains of the disease worldwide. The main debate here is how we can meet End TB’s vision of “A world free of TB: zero deaths, disease and suffering due to TB” without bargaining the inherent values and dignity of TB patients. It remains unclear how low-income countries would be able to meet one of the four key indicators of the strategy “Zero TB-affected families facing catastrophic costs due to TB by 2035” in situations where management of TB treatment still relies on directly observed therapy (DOT).

TB patients from the poorer segments of society are not benefiting from care delivery innovations: a contradiction between “Global Commitment to End TB” and “reality on the ground”. Management of their treatment still depends on DOT, where controversies are everywhere on its potential turning the End TB strategy to reality. DOT has been viewed as an efficient strategy for treatment adherence, while evidence has demonstrated that it poses an economic and social burden to TB patients living in low-income countries. Treatment of TB lasts for at least six months, where patients in the intensive phase of DOT need to collect their medication at healthcare facilities daily and swallow tablets under the direct observation of a healthcare worker throughout the intensive phase. This process challenges not only patients but also the healthcare system as it is labor-intensive to supervise the daily

treatment of large numbers of TB patients, which portend a dystopia in the epidemiology of the disease.

There is no single measurement strategy deemed a universal solution to improve adherence; however, DOT is yet the only option for management of TB treatment adherence in low-income countries, despite multi-method approaches used in high-income countries. There is a natural tendency to focus on patient-related domains as core determinants of TB treatment adherence, while for other chronic diseases, treatment relies on patient self-management, giving them freedom and ownership of their own and their communities' health. Adherence is a multidimensional phenomenon determined by the interplay of five sets of factors, of which patient-related factors are just one determinant (Figure 2). The common belief that patients are solely responsible for taking their treatment is misleading and most often reflects a misunderstanding of how other factors affect people's behavior and capacity to adhere to their treatment. It also places the burden solely on the patient and stigmatizes and demoralizes the patient who is deemed delinquent or a defaulter when this breaks down.

[figure not shown]

**Figure 2:** Five dimensions of adherence

Ethiopia, where the proposed study will be conducted, is among countries highly encumbered by the TB epidemic, and one of the least resourced in the world. According to the 2018 global TB report, there were 117,705 TB cases reported in the country, and of the annual \$93 million needed for TB care and control, the country's domestic contribution was only 11%. Despite TB care and treatment services being delivered free of charge, TB patients are facing out-of-pocket payments and income losses due to transportation, accommodation, and food to get treatment at healthcare facilities: tackling their adherence to treatment and forcing them to stop working, sell their properties, borrow money and reduce their overall income. These, in turn, are increasing rates of loss to follow-up, disease relapse, and drug resistance. The spread of TB due to patients traveling daily to healthcare facilities for medication is increasing the transmission potential of the disease, especially in the capital city Addis Ababa, where mobility is making the city crowded - as manifested through housing conditions and the public transport. Different studies conducted in Addis Ababa reported that TB patients consider their daily DOT visits as pointless, and providers see DOT as a very challenging strategy for TB patients. As a result, daily DOT survives in principle, while implementation is irregular as both TB patients and providers have uncertainties with it. Providers witness that TB patients prefer taking the tablets at home once they have the necessary advice and counseling. Patients complain that they travel for daily DOT on foot under exhaustive road conditions for up to two hours and 2.5 kilometer, taking several rests on their way because of their sickness. They spend much on transportation and some of them get fired from their job as they were absent for the daily DOT. Providers witness how patients are seen when they exhaust, and patients took their daily DOT with dissatisfaction. Some patients claim that once they are informed of the disease on day one, no one talks to them the following days and they just swallow the drug and go back. Besides, they face stigma on their way to daily DOT, and they change their name in the TB clinic for they do not want to be notified as TB patients. The challenge is similar in other parts of Ethiopia. According to the WHO 2018 report, TB treatment coverage in the country is 68%, which is minimum even to accommodate the current DOT need. The estimated percentage of MDR/RR TB cases is significantly higher in previously treated cases [14% (6.7–25)] than new cases [2.7% (1.6–4.1)]; which indicates that management of TB treatment under DOT is problematic in the country. There were 680 MDR/RR-TB and four XDR-TB laboratory-confirmed cases in the country in 2017, while many more were left undiagnosed due to limited availability of the service.

The Ethiopian national TB program adheres to the WHO End TB strategy for its TB functions. The national comprehensive TB guideline revised in 2016 standardizes the provision of one first-line anti-TB treatment regimen for both new and previously treated TB patients. The treatment is administered in two phases (Figure 3). The initial (intensive) phase consists of a fixed-dose combination of four drugs [(isoniazid (H), rifampicin (R), pyrazinamide (Z) and ethambutol (E), with 75/150/400/275 mg strength] to be taken for the first eight weeks for new cases. The second (continuation) phase consists of a fixed-dose combination (RH, with 75/150 mg strength) to be taken for four months for new cases, which may be extended to 10 months if the disease involves the central nervous system, bones or osteoarticular spaces. Management of treatment is entirely driven by DOT implementation principles and modalities.

[figure not shown]

 Bacteriologically confirmed TB patients include those diagnosed by a positive result on AFB microscopy, Xpert MTB/RIF Assay or culture;  DST may be performed from one sputum sample using Xpert MTB/RIF, LPA or conventional DST based on availability. Information on rifampicin may be enough to decide on Next Action.  if DST result shows resistance to INH but susceptible to Rifampicin; treat with RHZE for 9 months.

**Figure 3.** Flow Chart for Sputum AFB monitoring for bacteriologically confirmed PTB Patients

In Ethiopia, there have been no alternative TB treatment strategies to DOT to address patient-specific adherence barriers or challenges. This would have a significant impact on the End TB indicator of “Zero TB-affected families facing catastrophic costs due to TB by 2035”. Besides, Multidrug-resistant TB (MDR-TB) remains a serious issue in the country, with a high burden and transmission potential. Such evidence discloses the difficulty of Ethiopia in meeting the overall End TB strategy targets by 2035 unless significant investment is made to shape the current DOT strategy into a more advanced, technology-led, patient-centered strategy that could be responsive to individual patient preferences, needs and values.

The challenge with daily DOT is across sub-Saharan African countries, where DOT did not provide a significant solution to poor treatment adherence; instead, home and community-based therapies were shown to be possible alternative strategies to health facility DOT as studies held in Tanzania (50-52), Kenya, Zambia, South Africa, and Eritrea reported. The WHO 2018 Global TB Report showed that TB remains a leading cause of death in Africa. The continent accounts for a quarter of new TB cases and TB deaths worldwide, with 2.5 million people falling ill and 417,000 people dying from TB annually. Of the total TB patients co-infected with HIV globally, 72% of them live in Africa. The true burden of DR-TB in the continent is poorly described, with only 51% of countries having formal data in the WHO global TB database, where DR-TB is largely missed and this requires a major effort to achieve the 2035 targets.

